### **List of Abbreviations**

ASIA: American Spinal Injury Association (author of the ISNCSCI)

CPAP-Continuous positive airway pressure

CRF-Case report form

ISCOS: International Spinal Cord Society

REB: Research ethical board

SAE-A serious adverse event

SCI: Spinal cord injury

SRBDs: Sleep-related breathing disorders

VAS-Visual analog scale

Untreated sleep-related breathing disorders as an aggravating factor for neuropathic pain, cardiovascular dysfunction and spasticity following spinal cord injury

## Protocol Summary

### **Title**

Untreated sleep-related breathing disorders as an aggravating factor for neuropathic pain, cardiovascular dysfunction and spasticity following spinal cord injury.

### **Short title**

Sleep and secondary complications of SCI.

### **Type and phase of the study**

Cross-sectional, prospective study.

### **Sample Size**

N= 70 participants

### **Study Population**

Cervical/thoracic (injury level at C1 to T6), complete/incomplete (AIS A, B, C or D) SCI.

### **Accrual Period**

5-years

### **Study Duration**

May 1st 2019 to March 30th 2024 (36 months)

### **Study Intervention**

Home-based or hospital-unattended sleep test (using ResMed ApneaLink Air™) can be used as a practical, less expensive, validated and reliable surrogate for diagnosis of the SRBDs.

### **Primary Objective**

The linkage of untreated sleep-related breathing disorders (SRBDs) with neuropathic pain, cardiovascular dysfunction, and spasticity after SCI.

### **Exploratory Objectives**

Increase awareness of the SRBDs in the SCI population and among healthcare rehab professionals.

### **General Information**

#### ***1.1. Protocol title and date.***

***Untreated sleep-related breathing disorders as an aggravating factor for neuropathic pain following spinal cord injury.***

Protocol Version #7, March 23, 2021

Untreated sleep-related breathing disorders as an aggravating factor for neuropathic pain, cardiovascular dysfunction and spasticity following spinal cord injury

## **2.0 Background and Rationale**

### **2.1. Summary of previous findings**

The majority of individuals living with SCI experience chronic pain, including nociceptive and neuropathic pain. Nociceptive pain is caused by activation of the normal peripheral terminals of primary sensory neurons (“nociceptors”) that detect signs of actual or incipient tissue injury such as inflammation. Neuropathic pain is caused by injury or disease of the nervous system. SCI-induced neuropathic pain is considered a pathological, maladaptive consequence of damage to, and inflammation of, the central nervous system. Neuropathic pain occurs in 48% to 92% for individuals with SCI. Given that neuropathic pain is a frequent and usually permanent complication that is typically resistant to treatment, there is a great need for more effective approaches to manage SCI-induced neuropathic pain.

### ***Sleep disorders after SCI***

A variety of sleep disorders have been described in individuals with SCI including insomnia and sleep-related breathing disorders (SRBDs). In a review of 11 epidemiological studies, the mean prevalence of SRBDs was 6% in men and 4% in women in the general population. In comparison, SRBDs have been reported in 48% to 91% of individuals with tetraplegia, and 13% to 63% of individuals with paraplegia. Although the frequency of SRBDs after SCI is much greater than in the able-bodied population, this is still a largely under-studied secondary condition in the SCI population.

Untreated sleep-related breathing disorders as an aggravating factor for neuropathic pain, cardiovascular dysfunction and spasticity following spinal cord injury

In a recent qualitative study, 20 individuals with SCI voiced several barriers to good quality sleep including SCI-related dysfunction, care, sleep environment, pain, anxiety, and avoidance. In summary, “sleep problems, such as those described by participants in this study, have the potential to exacerbate several conditions that commonly occur after SCI and to significantly affect health-related quality of life.”

### ***Pain and sleep disorders***

Pain has a negative impact on sleep, and SRBDs can modulate changes in pain processing and sensitivity. In addition, several psychosocial factors (e.g., depression, anxiety) may exacerbate pain-related distress and disability in individuals with SCI, as has been reported in able-bodied people with SRBDs. Therefore, a bidirectional relationship between pain and sleep disorders in the SCI population is plausible, even though this clinically important association has not been properly addressed in the literature. Overall, at least two pathophysiological mechanisms are common to SCI-induced neuropathic pain and SRBDs: neuroinflammation and autonomic disturbances.

Overall, neuropathic pain, SRBDs and cardiovascular autonomic dysfunction are common complications after SCI that likely have interplay effects. However, the potential relationship between SRBDs and other secondary complications such as neuropathic pain and cardiovascular autonomic dysfunction in individuals with SCI have not been previously studied.

### ***Spasticity and sleep disorders***

Similar to neuropathic pain, spasticity is a common secondary complication after SCI that has been reported 40% to 60% of the individuals living with tetraplegia. It is still unclear how spinal cord injured people with an underlying sympathetic overactivity due to the loss of supraspinal control respond to those sympathetic and catecholaminergic changes during and after hypoxia. Also, the effects of sleep-related hypoxia on the sympathetically-denervated muscles of individuals with SCI remain unknown. Prior studies revealed an increased muscle sympathetic nerve activity under hypoxic conditions, which persisted even after removal of acute short-term exposure to intermittent hypoxia. While a previous study showed that muscle oxygenation is not significantly affected by intermittent hypoxia exposure, the prefrontal cortex suffered detrimental effects of hypoxia in the prefrontal cortex in able-bodied individuals. One may speculate that anterior horn cells may also be vulnerable to hypoxia and, hence, the response of the low motor neurons caudal to SCI may overreact (or underreact) to hypoxia and sympathetic drive. Of note, a recent systematic review on the physiologic and psychologic triggers for spasticity exacerbation found no previous study on the effects of SRBDs on the spasticity in individuals with SCI. Nonetheless, the potential effects of untreated SRBDs on the degree of spasticity after SCI have never been properly examined.

## **2.2 Rationale**

### ***Impact of outcomes on stakeholders***

It is anticipated that this original research project will confirm an association of untreated SRBDs with neuropathic pain, cardiovascular dysfunction and spasticity after SCI, which will have an impact on stakeholders as follows:

Untreated sleep-related breathing disorders as an aggravating factor for neuropathic pain, cardiovascular dysfunction and spasticity following spinal cord injury

- (i) For individuals living with SCI, proper management of SRBDs could have multiple important benefits. While this study will specifically explore reductions in neuropathic pain, cardiovascular dysfunction and spasticity, which would significantly improve quality of life for those with SCI, other important benefits of SRBDs (including reductions in daytime sleepiness, fatigue, mood disorder, cognitive effects) could be achieved. This may facilitate adherence to management of SRBDs which, according to the current standard of care, includes continuous positive airway pressure (CPAP) therapy for those individuals with SCI and moderate-to-severe SRBD. In this group of patients, CPAP therapy may become a non-pharmacological option for management of neuropathic pain and cardiovascular dysfunction when moderate-to-severe SRBD co-exists.
- (ii) Health care professionals will potentially add another non-pharmacological option (i.e., CPAP therapy) for management of neuropathic pain, cardiovascular dysfunction, and spasticity in those individuals living with SCI who are diagnosed with a moderate-to-severe SRBD. In addition, screening for SRBDs among individuals with SCI will likely improve due to the multiple benefits of the CPAP therapy.
- (iii) Administrators of rehabilitation facilities and policymakers will likely be encouraged to offer home-based or hospital-unattended sleep studies in the rehabilitation facilities that care for individuals living with SCI. Home-based or hospital-unattended sleep studies could be a more cost-effective strategy that favors early diagnosis and treatment of SRBDs, which may save hospital and healthcare costs.

#### ***Appropriate engagement of stakeholders***

In prior meetings with individuals living with SCI and representative consumers working at SCI Ontario, [name] and [name] confirmed their commitment to collaborate with us in this research project to refine data collection, interpretation and dissemination. Furthermore, healthcare professionals at Lyndhurst Centre were very engaged in the initial discussions about the potential outcomes of this study including the use of home-based or hospital-unattended sleep study, and the benefits of the CPAP therapy on neuropathic pain, cardiovascular dysfunction and spasticity after SCI. The investigators obtained full support for this research project.

#### ***Likelihood for knowledge uptake by target audience***

The potential benefits of this study have been briefly discussed with several patients with SCI, health care professionals, and administrators at Lyndhurst Centre. Overall, the comments were overwhelmingly supportive for this research project with particular reference to the benefits of using home-based or hospital unattended devices for the sleep studies in the SCI population. The possibility of CPAP therapy to concomitantly treat moderate-to-severe SRBD and improve neuropathic pain, cardiovascular dysfunction and spasticity is very appealing to individuals with living SCI.

#### ***Scientific***

Neuropathic pain, cardiovascular dysfunction, spasticity and SRBDs are common and clinically relevant secondary complications after SCI. According to the literature, at least two pathophysiological mechanisms are common to SCI-induced neuropathic pain and SRBDs: neuroinflammation and autonomic disturbances.

Untreated sleep-related breathing disorders as an aggravating factor for neuropathic pain, cardiovascular dysfunction and spasticity following spinal cord injury

SCI prompts systemic inflammation and neuroinflammation mechanisms associated with the production and release of proinflammatory cytokines. There is a growing body of evidence which suggests that neuroinflammation perpetuates into the chronic stage after SCI, similar to neuropathic pain. A neuroinflammatory response, mainly in the microglia and astrocytes, has been linked to hyperactivity in spinal pain pathways during SCI-induced pain. Also, astrocyte activation is a major constituent of neuroinflammation, and persistent activation of astrocytes contributes to chronic SCI-induced pain. Systemic inflammation and neuroinflammation also occur in able-bodied individuals with moderate-to-severe SRBDs. In a meta-analysis, the levels of systemic inflammatory markers (including CRP, TNF- $\alpha$ , interleukins 6 and 8) were found to be higher in able-bodied patients with SRBDs compared to control subjects. Moreover, this effect was proportional to the severity of SRBDs.

SCI can also result in autonomic dysfunction through the interruption of descending inhibitory pathways on cervico-thoracic and sacral preganglionic neurons (causing cardiovascular, urinary, sexual, and gastrointestinal complications). Individuals with SCI are predisposed to sympathetic overactivity due to the loss of supraspinal control. The interactions between autonomic nervous system and pain modulation are quite complex. Plastic reorganization of spinal autonomic circuitry caudal to the level of SCI enhance sympathetic anti-inflammatory reflex. Conversely, sympathetic stimulation can promote pro-inflammatory responses involving immune cells and release inflammatory mediators (including pain-related cytokines). Catecholaminergic and sympathetic alterations play a key role in the pathophysiology of cardiovascular disorders related to SRBDs in able-bodied people. It is still unclear how individuals with SCI respond to sympathetic and catecholaminergic challenges from hypoxia.

Prior studies revealed an increased muscle sympathetic nerve activity under hypoxic conditions, which persisted even after removal of acute short-term exposure to intermittent hypoxia. While a previous study showed that muscle oxygenation is not significantly affected by intermittent hypoxia exposure, the prefrontal cortex suffered detrimental effects of hypoxia in the prefrontal cortex in able-bodied individuals. One may speculate that anterior horn cells may also be vulnerable to hypoxia and, hence, the response of the low motor neurons caudal to SCI may overreact (or underreact) to hypoxia and sympathetic drive. Of note, a recent systematic review on the physiologic and psychologic triggers for spasticity exacerbation found no previous study on the effects of SRBDs on the spasticity in individuals with SCI. Nonetheless, the potential effects of untreated SRBDs on the degree of spasticity after SCI have never been properly examined.

Overall, neuropathic pain, cardiovascular autonomic dysfunction, spasticity and SRBDs are common complications after SCI that likely have interplay effects. However, the potential relationship between SRBDs and other secondary complications such as neuropathic pain and cardiovascular autonomic dysfunction in individuals with SCI have not been previously studied. By comparing SCI individuals without and with different degrees of SRBDs, this original study will fulfil the current knowledge gap in the literature and provide key information for a future clinical trial on the effects of CPAP therapy for better control of neuropathic pain and cardiovascular dysfunction in individuals living with SCI and SRBDs.

Untreated sleep-related breathing disorders as an aggravating factor for neuropathic pain, cardiovascular dysfunction and spasticity following spinal cord injury

## 2.3 Potential Risks and Benefits

### 2.3.1 Potential Risk

- **Risk to the participant**

Untreated sleep-related breathing disorders as an aggravating factor for neuropathic pain, cardiovascular dysfunction and spasticity following spinal cord injury

- a) There may be some minor discomfort from wearing the ApneaLink Sleep Breathing Monitor.
- b) There may be some minor disturbance of participant's usual sleep on the night that she/he is wearing the ApneaLink device.
- c) Participants may learn something about their sleep that they were unaware of, such as their probability of having a sleep disorder, which could cause some anxiety or discomfort. Those participants who are diagnosed with moderate-to-severe SRBD are expected to try on and adhere to CPAP therapy. If the participant refuse to be adherent to CPAP therapy, the healthcare professional caring for them is required by law to report the diagnosis to the Ministry of Transportation of Ontario that likely will suspend the participant's driving privileges.
- e) Blood collections can sometimes cause bruising, pain, or very rarely, loss of consciousness.
- f) Participants may learn something about their health related to abnormal blood test that they were unaware of, which may require further investigations and treatment by the participants' family physician; this could cause some anxiety or discomfort.

- **Risks to the community/public**

To the best of our knowledge: none.

- **Risks to the institution**

To the best of our knowledge: none.

### 2.3.2 Potential Benefits

- **Benefits to the participant**

The results of this study could help thousands of individuals living with SCI who experience neuropathic pain, cardiovascular dysfunction and SRBDs. We anticipate that, by confirming the association of neuropathic pain and cardiovascular dysfunction with SRBDs, this study will increase awareness of the early diagnosis and properly management of the SRBDs among individuals living with SCI. Also, a home-based sleep test is presumably a more feasible diagnostic tool for SRBDs in the SCI population than the conventional polysomnography that requires overnight stay in a sleep disorder clinic.

- **Benefits to the community/public**

The knowledge-to-action framework including two interacting phases (i.e., knowledge creation and action cycle) as described by Graham et al. will be adopted in this project. During knowledge creation, the knowledge producers should tailor their activities to the needs of potential users. During the action cycle, implementers and users are ought to work together for the success of the knowledge dissemination with focus on change healthcare practice and individuals' behaviors.

As proposed by [name] and endorsed by the Ontario Neurotrauma Foundation, an integrated knowledge transfer approach will be undertaken in this research project that has established a partnership with the SCI community from the initial steps to dissemination of the results. This innovative initiative enhances development of research projects that are meaningful for the consumers (i.e., individuals living with SCI) and other stakeholders. This approach presumably facilitates the dissemination of the study findings,

knowledge acquisition and, eventually, best practice implementation. We are thrilled that [name] and [name] have agreed to collaborate with us in this exciting and innovative research project. [name] has been actively assisting in the knowledge transfer of the CanPain SCI Clinical Practice Guidelines for management of neuropathic pain after SCI. [name] own experience as an individual living with SCI and neuropathic pain will also be a great asset in the conduction and dissemination of this research outcomes (see attached her letter of support). [name] has been leading the Ontario SCI Solutions Alliance for better access to best practice care for all individuals living with SCI. [name] will help us to recruit participants for the research project if necessary and, more importantly, he will enrich the knowledge dissemination of the study results with the objective of increasing awareness and facilitating access to early diagnosis and proper management of SRBDs, which can potentially improve SCI-induced neuropathic pain and cardiovascular dysfunction (see attached his letter of support from SCI Ontario).

Our research plan and budget includes key steps and corresponding financial support for the establishment of an integrated knowledge translation strategy in collaboration with [name] and [name], SCI Ontario, healthcare professionals, hospital administrators and policy makers.

- **Benefits to the Institution**

The linkage of SRBDs with neuropathic pain, cardiovascular dysfunction and spasticity as well as the feasibility of the home-based sleep test will be reported in different means. The knowledge transfer plan includes the following outputs: (i) A newsletter to the SCI community that will be prepared in collaboration with our partners from SCI Ontario; (ii) An original article that will be published in a peer-reviewed journal for dissemination in the scientific and medical community; and (iii) Conference abstracts and presentations that will be submitted to national and international scientific meetings targeting scientists, clinicians, other healthcare professionals, administrators and policy makers (e.g. ASIA, ISCoS). The anticipated outcomes will include: (a) Increase awareness of the SRBDs in the SCI population and among healthcare rehab professionals; (b) Facilitate access of individuals living with SCI to home-based sleep studies; and (c) Improve adherence of individuals living with SCI to diagnosis and treatment of SRBDs.

This project will include the following performance measurements:

- (1) **Outputs:**

- (i) A newsletter to the consumers to be disseminated to the Ontario SCI community;
- (ii) One manuscript submitted to a peer-reviewed medical journal;
- (iii) At least one abstract submitted to a national or international scientific meeting.

- (2) **Outcomes:**

- (i) Promoting the awareness of the association of SRBDs with neuropathic pain, cardiovascular dysfunction and spasticity after SCI among healthcare professionals by presenting the study results in conferences;
- (ii) Implementation of an outpatient/inpatient service for home-based or hospital-unattended sleep study at Lyndhurst Centre in collaboration with Sunnybrook for individuals with SCI;
- (iii) Disseminate the results on potential association of neuropathic pain/cardiovascular dysfunction and SRBDs to the consumers throughout a SCI Ontario newsletter.

Untreated sleep-related breathing disorders as an aggravating factor for neuropathic pain, cardiovascular dysfunction and spasticity following spinal cord injury

## **2.4 Description of the population to be studied**

This research project will include English-speaking adults (18 years of age or older) with subacute or chronic (at least 2 months after injury), cervical/thoracic (injury level at C1 to T6), complete or incomplete (AIS A, B, C or D) SCI who were not previously diagnosed and treated for sleep apnea.

## **2.5 Compliance with the protocol, ICH GCP and the regulatory requirements**

All the investigators involved in this protocol, under the supervision of the principal investigator [name], have committed themselves to follow the instructions established in the protocol, in compliance with the Good Clinical Practice and the policies established by UHN (e.g., respect of participants privacy and dignity, guidelines to record vital signs, responsibility in scientific research, etc.).

## **3.0 Study Objectives and Hypothesis**

### **3.1 Primary study objectives:**

- (1) To evaluate the potential association of neuropathic pain with SRBDs in individuals with SCI;
- (2) To study the potential relationship between cardiovascular autonomic dysfunction and SRBDs in individuals living with SCI;
- (3) To evaluate the potential association of spasticity with SRBDs after SCI.

### **3.2 Secondary study objectives:**

- (1) To confirm that a home-based sleep study is a feasible alternative for diagnosis of SRBDs in tetraplegics and paraplegics;
- (2) To compare the costs of a home-based sleep study with the conventional polysomnography in an overnight sleep clinic using cost-minimization analysis.

### **3.3 Study Hypothesis**

- (a) Individuals with SCI and untreated SRBDs more frequently develop more severe neuropathic pain;
- (b) Individuals with SCI and untreated SRBDs develop more significant cardiovascular dysfunction (i.e., reduced heart rate variation, more frequent episodes of autonomic dysreflexia during sleep);
- (c) Individuals with SCI and untreated SRBDs more frequently develop more severe spasticity.

## **4. Study Design**

### **4.1. Primary and secondary endpoints**

Each participant will undergo the following assessments:

#### **4.1.1 Primary Outcome measures:**

- a) The presence and intensity of neuropathic pain as assessed using the Visual Analog Scale (VAS; range: 0 to 100) and daily amount of analgesics (pregabalin, neurontin, opioids, etc.);

Untreated sleep-related breathing disorders as an aggravating factor for neuropathic pain, cardiovascular dysfunction and spasticity following spinal cord injury

- b) The cardiovascular activity during sleep based on the peripheral arterial tone and overall heart rate variability as recorded using the Bittium Faros™ 180 device and Caretaker™ Medical cNIBP monitor device;
- c) The number of episodes of autonomic dysreflexia during sleep and their association with apneas and hypopneas by combining the recorded data from the ApneaLink™, Bittium Faros™ 180 device and Caretaker™ Medical cNIBP monitor devices;
- d) The degree of spasticity in the upper and lower limbs as assessed using the Modified Ashworth Scale;
- e) Serum CRP level.

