Those individuals with clinical warning signs for SRBDs will undergo a home-based sleep study using the ApneaLink™ (Picture 1) device to confirm the diagnosis of SRBD (n=30). Based on the results of the home-based sleep study, individuals with SRBD will be grouped into mild (n=10), moderate (n=10) and severe sleep apnea (n=10). Also, individuals without clinical warning signs for SRBD will undergo a home-based sleep study using ApneaLink™ in order to identify 10 study participants without SRBDs (“control cases”).

All participants will also undergo cardiovascular evaluation during sleep using the Bittium Faros™ 180 (Picture 3) and Caretaker™ Medical cNIBP monitor (Picture 2) devices to assess sympathetic activity during sleep in all study participants (n=40). All participants will be examined with regards to their degree of spasticity as assessed using the Modified Ashworth Scale. Also, all participants will undergo laboratory blood tests to measure their serum CRP level.

Furthermore, an economic analysis will be undertaken in order to compare the costs of the home-based sleep study with the conventional polysomnography in a sleep clinic. For this purpose, the costs of the home-based sleep test will be estimated based on our experience during this study. The costs of the conventional polysomnography will be obtained from the sleep clinic at Sunnybrook Hospital where [name], co-investigator in this study, works. The professional and technical fees will be derived from the Ontario Health Insurance Plan (OHIP) – Schedule of Benefits, Physician Services.

All participants who are diagnosed with moderate-to-severe SRBDs during the study will be referred to [name] or other sleep specialist for consultation and CPAP therapy. Also, study participants whose CRP levels are greater than 10 mg/L (normal range up to 3 mg/L) will be immediately referred to their family physician (or emergency if symptoms or signs of systemic infection) for further investigations and treatment because a CRP greater than 10 mg/L is suggestive of infection or primary inflammatory disease.

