## **7. Statistics**

The baseline characteristics and outcomes measures among the four study groups will be analyzed using the Kruskal-Wallis test (non-parametric data) or ANOVA (parametric data). Study groups will also be compared using Fisher exact test regarding categorical variables. The costs of the home-based sleep study will be compared to the costs of the polysomnography using Mann-Whitney U test. Sample size and feasibility: Using pain (VAS) as the primary outcome measure, an estimated sample size of 10 subjects per group is required to detect a "minimal clinically important difference" of at least 25 mm in the VAS with a minimum power of 90% and a significance of 5% for 2-sided comparison tests.

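### Overall heart rate variability during sleep includes any swings at breathing events, so with a total-variability index a true reduction in SRBD can be diluted and, if swings are large, reversed

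*Protocol*

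**What the plan says.** Section 3.3, hypothesis (b), fixes a direction. Untreated SRBD is expected to bring "reduced heart rate variation, more frequent episodes of autonomic dysreflexia during sleep".

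Section 4.1.1, primary outcome (b), is "The cardiovascular activity during sleep based on the peripheral arterial tone and overall heart rate variability". The part at issue here is "overall heart rate variability as recorded using the Bittium Faros™ 180 device". It names no index and no recording window, and it does not distinguish breathing events from the rest of the recording. Outcome (c), the count of dysreflexia episodes, is the only one tied in time to respiratory events: the plan will study "their association with apneas and hypopneas by combining the recorded data from the ApneaLink™" and the two cardiovascular devices.

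Section 4.3 gives the purpose of the cardiovascular recordings as "to assess sympathetic activity during sleep in all study participants (n=40"). It forms the groups from the sleep test: "individuals with SRBD will be grouped into mild (n=10), moderate (n=10) and severe sleep apnea (n=10"), plus controls without SRBD. Under section 7, outcomes in the four groups "will be analyzed using the Kruskal-Wallis test (non-parametric data) or ANOVA (parametric data").

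On the physiology in this population, section 2.2 (Scientific) says: "It is still unclear how individuals with SCI respond to sympathetic and catecholaminergic challenges from hypoxia".

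**The concern.** The events that define the groups occur inside the recording that produces the outcome. If an apnea slows the heart and its end speeds it up, a night with many apneas contains a cyclic component in the beat intervals. In a total-variability index that component raises the value, and it does so more in the moderate and severe groups. Hypothesis (b) expects the value to be lower in those groups.

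At stake is how one primary outcome is interpreted. A real loss of variability could appear as no difference. A higher value in severe SRBD could be misread as healthier cardiovascular control. The direct group comparison in section 7 cannot separate the two sources.

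**Working it through.** The Protocol gives no figure for heart rate variability, so there is none to reproduce. Its only sample-size figure concerns pain and does not bear on this point. Every number below is an assumption, used to show direction and rough size.

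**Formula.** Take the overall index to be the SD of beat intervals. Let s be the SD without the swing, A the half-amplitude of a sinusoidal swing during events, and f the share of the recording spent in events. If the swing is uncorrelated with the background:

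overall SD = √(s² + f·A²/2)

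The added term is never negative, and it grows with the event rate through f.

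**Illustration, severe group.** Controls 60 ms; severe SRBD background 48 ms (20% lower); 30 events/h of 45 s.

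f = 30 × 45 / 3600 = 0.375

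| Swing (±A) | Added variance 0.375·A²/2 | Overall SD | Against 60 ms |
|---|---|---|---|
| 50 ms | 469 ms² | √(2304 + 469) = 52.7 ms | 12% lower |
| 100 ms | 1875 ms² | √(2304 + 1875) = 64.6 ms | 8% higher |
| 150 ms | 4219 ms² | √(2304 + 4219) = 80.8 ms | 35% higher |

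The sign changes where 0.375·A²/2 = 60² − 48² = 1296, so A = √6912 ≈ 83 ms, or about 166 ms peak to peak.

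**Other event rates.** With a 50 s cycle, f = events per hour × 50 / 3600. Break-even peak-to-peak swing = 2√(2(s₀² − s²)/f), where s₀ is the control SD. The range column uses control SDs of 60 to 100 ms and true reductions of 10% to 30%.

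| Events/h | f | Break-even at 60 against 48 ms | Range |
|---|---|---|---|
| 40 | 0.56 | 137 ms | 99 to 271 ms |
| 22 | 0.31 | 184 ms | 134 to 365 ms |
| 10 | 0.14 | 273 ms | 198 to 542 ms |

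Reversal needs the smallest swing at high event rates and the largest at low ones. Dilution occurs with any swing.

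**A beat-to-beat index.** In a simulated beat series (control SD 60 ms, background 48 ms, 40 events/h), peak-to-peak swings of 100, 150 and 200 ms gave overall SDs of 54.8, 61.8 and 72.0 ms. RMSSD in the same series was 10.1, 10.4 and 11.2 ms against 12.1 ms in controls, so it stayed in the hypothesised direction.

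RMSSD is still diluted. A 50 s sinusoid sampled every 0.9 s contributes f·(A × 2π × 0.9/50)²/2 = f·(0.113A)²/2 to squared RMSSD. The gap to fill is 12.1² − (0.8 × 12.1)² = 52.7. With f = 0.556, A ≈ 122 ms, or about 244 ms peak to peak, against 137 ms for the SD. The sign therefore depends on the index, which section 4.1.1 leaves open.

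**How much event-free time remains.** At 30 events/h of 45 s, evenly spaced events leave gaps of 120 − 45 = 75 s. A 1-minute window fits; 2-minute and 5-minute windows do not. With randomly timed events, the share of windows of w seconds that are event-free is exp(−30/3600 × (w + 45)): 42% at 60 s, 25% at 120 s and 5.6% at 300 s.

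**The case against.** The strongest reply is that the premise is not in the documents. No section describes a heart-rate swing at apneas, and section 2.2 calls the response to hypoxia after SCI unclear. In C1-T6 injury, with disrupted autonomic control, the swing could be small. This stands, and it rules out any claim that the endpoint will move the wrong way.

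Second, the calculation assumes an SD-type index over the whole recording, whereas the plan says only overall and during sleep. Index and window are details that a statistical analysis plan may settle. This stands in part: leaving them open is not itself a fault. But the Protocol itself chose overall variability and itself stated the direction, and total variability over the recording is the natural reading of its words.

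Third, background autonomic tone need not be the only target. Section 4.3 speaks of sympathetic activity during sleep, and outcome (c) deliberately looks at events. Peripheral arterial tone and dysreflexia counts also bear on hypothesis (b). This is fair, and it argues for keeping the overall measure.

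Fourth, replacing it with 5-minute event-free windows would leave few windows in severe SRBD (5.6% in the random-timing case), with missingness driven by the grouping variable. This also stands.

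A reader might infer that outcome (b) cannot be interpreted, or that variability is certain to be higher in severe SRBD. The documents support neither, because the swing size is unknown and the sign depends on the index.

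**Conclusion.** The point holds as a conditional one. The Protocol pairs a directional hypothesis of reduced heart rate variation with an outcome that does not separate event time from event-free time, and compares groups ordered by event severity. For a total-variability index, any swing at breathing events works against the hypothesised direction, increasingly with severity.

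Under the assumed values, a true 20% deficit at 30 events/h shrinks to 12% with a ±50 ms swing and changes sign beyond about ±83 ms. At 10 events/h with a 50 s cycle, reversal would need a peak-to-peak swing of about 200 to 540 ms, so it is least plausible in mild disease. The conclusion rests on three assumptions: that swings occur in this population, that they are roughly uncorrelated with the background, and that the index is of the SD type. RMSSD is considerably less affected, though not immune.

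The point affects one of several primary outcomes. It warrants an inexpensive clarification, not a redesign.

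**What to change.** In section 4.1.1(b):

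- Name the heart rate variability index.
- Report it from segments free of ApneaLink-scored apneas and hypopneas, alongside overall variability. Use segments short enough for severe participants to contribute, for example 1 to 2 minutes, with an index valid at that length. The window calculation favours the shorter end.
- Report the number of usable segments per participant and per group.
- State that a higher overall value in SRBD groups will not be read as better autonomic function unless the event-free measure agrees.

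No new recording is needed, because outcome (c) already requires combining the ApneaLink and Faros data. The cost is some extra processing. The limitation is that event-free segments will be fewer, and possibly unrepresentative, in severe SRBD. That is why the two measures should be reported together, neither replacing the other.
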